### Randomization

To reduce the potential for contamination, the unit for randomization will be the clinician. Clinicians will be randomized 2:1 to either the intervention (12 clinicians:72 adolescents; to have DIALOG-A sessions once per month for 6 months) or to the treatment-as-usual control group (6 clinicians:36 adolescents; appointments scheduled as and when needed, without DIALOG-A or specific assessments). For existing patients, who are already on the caseload, adolescent participants will be recruited and baseline assessments conducted prior to their clinician being randomized. Individuals who are new to the service and are not on the existing caseload of a clinician will be randomly assigned to either the intervention or control arm and then to an appropriate clinician, following completion of the baseline measures. We will record the number of adolescent participants who are recruited and individually randomized.

Clinicians and adolescents will not be blinded to allocation due to the nature of the intervention. However, to reduce bias, randomization will be carried out by a blinded independent statistician at the Unit for Social and Community Psychiatry, Wolfson Institute of Population Health, Queen Mary University of London. Baseline data collection will occur before randomization, and all research assistants involved in outcome data collection will be blinded to allocation. We will additionally record the number of postrandomization recruits; for example, individuals who were recruited after their clinician has been randomized.

### Proposed Sample Size

A formal sample size calculation was not conducted as the primary objective is to collect data required for a full trial protocol, including the information needed for sample size calculation. Estimates for adequate sample sizes for exploratory trials range from 24 to 50 per arm, with at least 30 individuals required to estimate the SD of the outcomes. This exploratory trial will include 108 patients to provide usable estimates from each site. Unbalanced 2:1 randomization favoring the intervention will ensure sufficient data about the experience with the DIALOG-A intervention. Randomization will be stratified by the site to include 12 clinicians at the 3 study sites in Bogota and 6 at the study site in Duitama to reflect differences in population size and available resources.

### Quantitative Data

All participants (clinicians and adolescents) will be asked to complete a sociodemographic questionnaire at baseline. Clinicians will be asked to rate the Clinical Global Impression questionnaire after every appointment.

The primary outcomes will be collected at 6 months, with a further follow up of 9 months post randomization—these include symptoms of depression measured using the 8-item Patient Health Questionnaire [25] and symptoms of anxiety measured using the 7-item Generalized Anxiety Disorder scale [26].

All secondary outcomes will be collected at baseline, 6 months, and 9 months (unless otherwise stated)—these include quality of life measured using the Manchester Short Assessment of Quality of Life [27], mental health symptom levels measured using YP-CORE [28], social support measured using the Multidimensional Scale of Perceived Social Support [29], empowerment measured using the Youth Efficacy/Empowerment scale [30], self-esteem measured using the Rosenberg Self-Esteem Scale [31], and economic outcomes measured using a modified Client Service Receipt Inventory [32].

In addition to the outcome data described above, we will collect process measures, including the number of DIALOG-A interventions performed, the date and duration of those sessions, the scores obtained on the DIALOG scale within each session, key topics discussed during the 4-step approach, and what actions were agreed upon. The DIALOG-A app on the tablet is able to capture the data required. This information will be synchronized to a server that the research team can access.

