Within a cluster randomized controlled trial (RCT) conducted across 6 European countries, regular use of the initial form of DIALOG+ over a year led to a better quality of life, fewer unmet needs, and higher treatment satisfaction for patients with psychosis. Following further modifications, DIALOG+, delivered once per month over 6 months, was compared to an active control in a pragmatic RCT involving 49 clinicians and 178 patients diagnosed with psychosis. Patients in the experimental group had a significant improvement in quality of life and lower general psychopathological symptoms after 3, 6, and 12 months. They also had fewer unmet needs and a better objective social situation. The effect size for improvements in quality of life ranged from 0.30 (95% CI 0.02-0.58) at 3 months to 0.32 (95% CI 0.06-0.58) at 12 months. Furthermore, DIALOG+ saved the National Health Service £1345 (US $1610.16) per patient, mainly due to fewer inpatient days required by the experimental group [17-19]. However, research has not assessed whether the intervention may also be effective for adolescents with common mental disorders.

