### Quantitative Data Analysis

The number of approached and screened participants, those who refused participation, and those who could not be contacted will be recorded. The analysis will assess the number of intervention sessions received by participants and will collect data on dropouts (including reasons for dropping out, if available) from treatment, which will inform the assessment of the acceptability of the DIALOG-A intervention.

Descriptive statistics will be reported for sociodemographic data for all participants. Nominal and ordinal data will be presented as proportions (frequencies), whereas continuous variables will be described using measures of central tendency and those of variability. The latter will be selected in accordance with observed data distributions (parametric or nonparametric), which will be evaluated through normality tests and histograms (probability functions). To assess the effectiveness of the intervention, means and SDs (or median and IQR values) over the 3 time points (baseline, 6 months, and 9 months) will be calculated, and analysis will test the significance of the differences between the means (or other parameters) of outcomes measured. The primary outcome will be the scores on the 8-item Patient Health Questionnaire and the 7-item Generalized Anxiety Disorder scale at 6 months. Mixed effects multivariable logistic regression analysis will be conducted to assess the effect of the intervention on the primary outcome, while controlling for clustering. A full analysis plan will be developed prior to data analysis, which will consider which covariates should be adjusted for in the model, along with methods for dealing with missing data. Quantitative data analysis will be conducted using Stata (version 17; StataCorp).

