### Strengths and Limitations

This study is the first to test the effect of DIALOG-A as a tool for use in primary care services for adolescents with depression and anxiety. One strength is the pragmatic design, which will enable us to adapt to the different logistics in the centers included in this RCT. One limitation, however, is that due to the characteristics of the intervention, blinding of the adolescent participants and clinicians will not be possible, which may result in the introduction of bias and a placebo effect. Additionally, the study is an exploratory study with unequal randomization (2:1 favoring the intervention). Although this will enable us to estimate potential interventions effects, a definitive trial will be needed to establish efficacy.

A potential benefit is that overall, the study has the potential to adapt a low-cost resource-orientated intervention for use in a vulnerable adolescent population. Additionally, for adolescents who will be involved in the testing of the modified intervention (DIALOG-A), this might lead to improved quality of life, social functioning, and symptoms. The RCT will also benefit the clinicians involved as they will be provided with training and supervision to enable them to implement the intervention. If results are successful, DIALOG-A can be implemented in the routine care of these adolescents in Colombia as it does not need the setting of new services or restructuring of preexisting organizations and is of low cost.

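### The distribution-driven choice between mean and median covers the economic outcome without exemption and would very likely give medians, which do not estimate cost per patient

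*Protocol article*

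**What the plan says.** Under Quantitative Data, the last secondary outcome listed is "economic outcomes measured using a modified Client Service Receipt Inventory", collected at baseline, 6 months and 9 months. The Results section says that changes in economic outcomes will be reported.

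Quantitative Data Analysis sets out how summaries of continuous variables are chosen: "The latter will be selected in accordance with observed data distributions (parametric or nonparametric), which will be evaluated through normality tests and histograms". For the comparison over time it says that "means and SDs (or median and IQR values) over the 3 time points (baseline, 6 months, and 9 months) will be calculated", and that "analysis will test the significance of the differences between the means (or other parameters) of outcomes measured". The mixed-effects regression in the same section is stated for the primary outcome only. The section defers to a full analysis plan and names two matters for it, covariates and missing data.

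The Introduction reports that DIALOG+ saved £1345 per patient in an earlier trial, "mainly due to fewer inpatient days required by the experimental group". Proposed Sample Size says that the main purpose is to collect what a full trial protocol needs, and refers to the number of individuals required to estimate the SD of the outcomes.

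**The concern.** The outcome sentence allows either summary, and the only criterion the article gives for choosing is the shape of the data. That is defensible for a symptom score. For a cost it lets the distribution decide what is being estimated. A health service pays the mean cost times the number of patients, and no budget figure can be recovered from a median.

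Service use usually shows many low values and a few very large ones, so a normality check would point to the median. The saving cited in the Introduction came mainly from inpatient days, which are expensive contacts of the kind a median barely registers. If the report gives only medians and IQRs, readers cannot compare it with that saving, and the designers of a full trial lack the mean and SD of cost.

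**Working it through.** The article gives no cost distribution, unit cost or contact frequency, and states that no formal sample size calculation was done. There is no figure of the plan's own to reproduce. What can be checked is how far mean and median part company under assumed costs.

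**Inputs from the article:** 72 intervention and 36 control adolescents; 12 and 6 clinicians.

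**First assumed model.** Routine cost is exponential with mean 1 unit. A fraction p of adolescents also has a costly contact averaging 20 units.

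- Mean = 1 + 20p.
- Treating every costly contact as lying above the median, the median m solves (1 − p)(1 − e^−m) = 0.5, so m = −ln[1 − 0.5/(1 − p)].
- At p = 0.10: mean = 1 + 2 = 3.0; m = −ln(0.4444) = 0.811.
- At p = 0.05: mean = 1 + 1 = 2.0; m = −ln(0.4737) = 0.747.
- Change in mean = (2.0 − 3.0)/3.0 = −33%. Change in median = (0.747 − 0.811)/0.811 = −8%.

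The same formulas over a range of frequencies:

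| p, control to intervention | Mean | Change | Median | Change |
|---|---|---|---|---|
| 5% to 2% | 2.0 to 1.4 | −30% | 0.747 to 0.714 | −4% |
| 10% to 5% | 3.0 to 2.0 | −33% | 0.811 to 0.747 | −8% |
| 15% to 8% | 4.0 to 2.6 | −35% | 0.887 to 0.784 | −12% |
| 20% to 10% | 5.0 to 3.0 | −40% | 0.981 to 0.811 | −17% |

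**Second assumed model, simulated.** Routine cost is lognormal with mean 100 and log-SD 0.3, 0.5 or 0.8. A costly contact averages 2000. Each scenario has 4,000 trials of 72 vs 36, without clustering. True means are 100 + 2000p. Ranges run over the three log-SDs, and differences are intervention minus control.

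| p, control vs intervention | True difference in means | Average difference in medians | SD of estimated mean difference | Welch t significant | Mann-Whitney significant |
|---|---|---|---|---|---|
| 5% vs 2% | 140 − 200 = −60 | −1.3 to −3.1 | 100 to 103 | 1.4% to 2.4% | 5.1% to 5.6% |
| 10% vs 3% | 160 − 300 = −140 | −3.1 to −7.4 | 132 to 134 | 7.0% to 7.9% | 9.5% to 9.6% |
| 15% vs 5% | 200 − 400 = −200 | −4.9 to −12.1 | 158 to 163 | 13.3% to 14.8% | 13.7% to 13.8% |

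- A Shapiro-Wilk test on the pooled data rejected normality in 99.7% to 100% of trials. A rule driven by normality tests would therefore almost always point to the median.
- At 10% vs 3% the mean falls by 140/300 = 47%. The population medians are about 95 vs 90 (log-SD 0.5) or 81 vs 75 (log-SD 0.8).
- The mean difference carries the saving, but imprecisely. At 10% vs 3%, 1.96 × 133 = 261, so a rough interval around −140 runs from −401 to 121. Clustering by clinician would usually widen it.

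**The case against.** The strongest reply is that this reads too much into general wording. The normality-test rule stands among sentences on descriptive statistics, histograms count as well as tests, and the outcome sentence is framed around effectiveness. The article never says outright that costs will be calculated. A full analysis plan is promised, and how a secondary economic outcome is summarised is often left to such a plan. These points stand as limits: the rule would very likely lead to medians, but this is not certain. They do not remove the concern. The sentence refers to the outcomes measured, exempts none, and is the only analysis stated for the secondary outcomes. What is at issue is a rule the article states, and the matters it defers do not include the parameter to be compared.

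A reader might infer that rank tests will be used. The article names none: the word nonparametric describes the data distribution, and the test is of means or other parameters, which permits a rank test without requiring one.

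A reader might also infer that the rule hides a saving that a test of means would detect. The simulation does not support that. Welch's t was significant in about 1% to 15% of trials and Mann-Whitney in about 5% to 14%. With 108 adolescents neither finds such a saving reliably.

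The cost inputs are fairly challenged too. The inpatient saving came from patients with psychosis, whereas this trial enrols adolescents aged 13 to 16 in primary care and excludes severe mental illness. Costly contacts may be rarer here than assumed. The outcome is also secondary in an exploratory trial, and means can still be calculated later from the retained data.

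**Conclusion.** The point holds as a low-severity improvement. As written, the mean-or-median rule reaches the economic outcome and would very likely yield a summary that does not estimate cost per patient. Under the first assumed model the mean falls by 30% to 40% while the median falls by 4% to 17%. The second model shows the same direction in every scenario with fewer costly contacts in the intervention arm. These sizes rest on assumed frequencies and costs. The conclusion needs only that costs are right-skewed and that any difference lies largely in infrequent, expensive contacts.

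The loss is in the quantity reported, not in power. It still matters here, because the trial exists to supply estimates for a full trial, and because the earlier saving is expressed per patient. The remark in Strengths and Limitations that DIALOG-A "does not need the setting of new services or restructuring of preexisting organizations and is of low cost" is not said to rest on this comparison, so the point does not undermine that statement.

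**What to change.** In Quantitative Data Analysis, and in the full analysis plan, exempt any cost derived from the Client Service Receipt Inventory from the mean-or-median rule. Whatever the distribution, report the arithmetic mean cost per adolescent and its SD by arm. Report the difference in means with an interval that allows for clinician clusters and skewness, for example by resampling clinicians within arm or by a t interval on clinician means. With only 12 and 6 clinicians any such interval is approximate. Medians and IQRs may be added as description only.

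This takes one sentence and no new data. The drawback is a wide interval for the cost difference, which reflects what a trial of this size can say.

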### Qualitative Data

A subset of adolescent participants (n=20) and all clinicians (n=12) randomized to the intervention arm will be invited to complete an in-depth qualitative interview after the 6-month assessments (time point at the end of the intervention period) to capture and discuss their experience of delivering or receiving DIALOG-A. Interviews will focus on the barriers and facilitators of attending intervention sessions, suggested adaptations, trial procedures, practical implementation in the study sites, and potential processes of change. These interviews will be audio-recorded, transcribed verbatim, and further analyzed.

### Statistical Analysis

The analysis of data will be discussed and agreed upon with the local and international research teams, with a statistical analysis plan developed by the statistician and signed off by trial steering committee. The local research team will take a leading role in the management and analysis of the data. Data analysis will not be conducted prior to signing off and blinding of the members of the research team, including the statistician responsible for the analysis, who will remain blinded throughout.

### Quantitative Data Analysis

The number of approached and screened participants, those who refused participation, and those who could not be contacted will be recorded. The analysis will assess the number of intervention sessions received by participants and will collect data on dropouts (including reasons for dropping out, if available) from treatment, which will inform the assessment of the acceptability of the DIALOG-A intervention.

Descriptive statistics will be reported for sociodemographic data for all participants. Nominal and ordinal data will be presented as proportions (frequencies), whereas continuous variables will be described using measures of central tendency and those of variability. The latter will be selected in accordance with observed data distributions (parametric or nonparametric), which will be evaluated through normality tests and histograms (probability functions). To assess the effectiveness of the intervention, means and SDs (or median and IQR values) over the 3 time points (baseline, 6 months, and 9 months) will be calculated, and analysis will test the significance of the differences between the means (or other parameters) of outcomes measured. The primary outcome will be the scores on the 8-item Patient Health Questionnaire and the 7-item Generalized Anxiety Disorder scale at 6 months. Mixed effects multivariable logistic regression analysis will be conducted to assess the effect of the intervention on the primary outcome, while controlling for clustering. A full analysis plan will be developed prior to data analysis, which will consider which covariates should be adjusted for in the model, along with methods for dealing with missing data. Quantitative data analysis will be conducted using Stata (version 17; StataCorp).

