### Participants

#### Inclusion Criteria

The inclusion criteria for clinicians will be as follows: (1) being aged 18 years or older, (2) having a medical qualification as a general practitioner or pediatrician, (3) having regular contact with adolescent patients with anxiety and depression, (4) having at least 3 months of experience in working with adolescents, and (5) having no plans to leave their current position within the next 6 months.

The inclusion criteria for adolescents will be as follows: (1) being aged 13 to 16 years; (2) currently experiencing anxiety and depression, which is defined as a cutoff score of ≥7 on the Self-Reporting Questionnaire [23]; and (3) having the capacity to provide informed assent.

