## Results

Trial recruitment was completed toward the end of October 2022, and follow-up is expected to last through October 2023. We anticipate the outcomes of the trial will be reported by mid-2023 and the follow-ups by early 2024. The primary outcomes will be changes in depression [25] and anxiety [26] symptoms and the secondary outcomes will include changes in quality of life [27], mental health symptom levels [28], perceived social support [29], empowerment [30], self-esteem [31], and economic outcomes [32]. Furthermore, we will report on dropout rates and adverse events which take place during the trial.

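### The primary outcomes are PHQ-8 and GAD-7 scores, but the model named for them is a mixed-effects logistic regression, and no binary or ordinal endpoint is defined on either scale

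*Protocol article*

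**What the plan says.** The Quantitative Data Analysis section of the protocol article fixes the outcome first: "The primary outcome will be the scores on the 8-item Patient Health Questionnaire and the 7-item Generalized Anxiety Disorder scale at 6 months". The next sentence fixes the model: "Mixed effects multivariable logistic regression analysis will be conducted to assess the effect of the intervention on the primary outcome, while controlling for clustering".

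The other descriptions of the outcome are numeric too:

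- Just before these two sentences, the same section plans means and SDs (or medians and IQRs) at baseline, 6 and 9 months, and says that "analysis will test the significance of the differences between the means (or other parameters) of outcomes measured".
- The Quantitative Data section lists "symptoms of depression measured using the 8-item Patient Health Questionnaire" and, in the same way, anxiety symptoms on the GAD-7.
- The Results section says: "The primary outcomes will be changes in depression [25] and anxiety [26] symptoms".
- The Proposed Sample Size section gives as its rationale the number of individuals needed to estimate the SD of the outcomes.

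A full analysis plan is to follow, "which will consider which covariates should be adjusted for in the model, along with methods for dealing with missing data". Those are the only two items named for it.

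**The concern.** Logistic regression in its usual form models the probability of a yes/no event. A symptom score, or a change in one, is not such an event. To run the named model, someone must first turn each score into a binary variable, and the article gives no caseness, response or remission rule for either scale. Its only cut-off is for eligibility, on a different instrument: "which is defined as a cutoff score of ≥7 on the Self-Reporting Questionnaire".

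The target of estimation is therefore open. The model sentence points to an odds ratio at an unstated threshold, while the outcome sentence and the descriptive plan point to a difference in mean scores. These are different quantities with different precision.

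The Proposed Sample Size section says the trial is meant to supply the information for a full trial, including its sample size calculation. For a definitive trial on these scales, a mean difference adjusted for clustering and an ICC on the score scale are useful inputs. The named model yields neither.

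**Working it through.** **1. Text check.** Outcome: scores at 6 months, or changes in symptoms. Descriptive plan: means and SDs, with differences between means. Model: logistic. Thresholds on PHQ-8 or GAD-7: none. Items named for the later plan: covariates and missing data, so neither the model family nor a cut-point is expressly deferred. The logistic sentence is the one that does not fit the rest.

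**2. Design inputs (Randomization section).** 12 + 6 = 18 clinicians; 72 + 36 = 108 adolescents; 72/12 = 36/6 = 6 per clinician. The article reports no power, alpha, effect size, SD or ICC and says that no formal calculation was done, so there is no figure to reproduce. Everything below rests on assumptions: a two-sided 5% test, approximately normal scores, and the ICC, effect size and split shown.

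**3. Information lost by a cut-point.** Let p be the share on one side of the cut and z_p the matching normal quantile. The efficiency of the binary version relative to the score is φ(z_p)² / [p(1 − p)].

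| Split | φ(z_p) | Efficiency | Loss | 108 patients are worth |
|---|---|---|---|---|
| 50/50 | 0.399 | 0.1592/0.25 = 0.637 | 36% | 69 |
| 30/70 | 0.348 | 0.1209/0.21 = 0.576 | 42% | 62 |
| 20/80 | 0.280 | 0.0784/0.16 = 0.490 | 51% | 53 |
| 10/90 | 0.175 | 0.0308/0.09 = 0.342 | 66% | 37 |

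**4. Power on the score.** Assume ICC 0.05 and a true effect of 0.5 SD, without baseline adjustment. Design effect = 1 + (6 − 1) × 0.05 = 1.25. Standard error = √[1.25 × (1/72 + 1/36)] = 0.228 SD. Noncentrality = 0.5/0.228 = 2.19. With 18 − 2 = 16 degrees of freedom, power is 0.539, about 54%.

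**5. Power on the binary version, same assumptions.** The ICC is rescaled from the latent score to the binary scale (about 0.02 to 0.03).

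- 50% of controls above the cut: intervention share Φ(0 − 0.5) = 30.9%, difference 0.191, standard error 0.107, noncentrality 1.79, power about 39%.
- 30% of controls above the cut: intervention share Φ(−0.524 − 0.5) = 15.3%, difference 0.147, standard error 0.093, noncentrality 1.58, power about 32%.

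**6. Range over other assumptions.** This table uses a simpler normal reference and the same design effect for both versions, with 20% to 80% of controls above the cut. The normal reference is why the score row for 0.5 SD and ICC 0.05 reads 59% and not 54%.

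| Effect (SD) | ICC | Score | Binary |
|---|---|---|---|
| 0.5 | 0 | 69% | 38% to 49% |
| 0.5 | 0.05 | 59% | 32% to 41% |
| 0.5 | 0.10 | 52% | 28% to 36% |
| 0.3 | 0.05 | 26% | 14% to 18% |
| 0.8 | 0.05 | 94% | 58% to 79% |

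The binary version has less power in every row. How much less depends on inputs that the article does not give.

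**The case against.** The strongest reply is that this is an exploratory trial with no power target, that a full analysis plan will follow, and that the wording may be a slip which that plan puts right. Much of this stands as a limit on the harm. It does not remove the mismatch, because the article names the model family itself. A plan that follows the article inherits the problem, and one that uses a linear model departs from the published text and must say so.

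Four stronger readings are tempting, but the document does not support them.

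- **That the trial would lose its SDs.** It would not: means and SDs at all three time points are planned separately. What would be missing is the clustering-adjusted mean difference and the ICC on the score scale.
- **That the cut-point would be picked after seeing results.** The Statistical Analysis section requires the steering committee to sign off the plan before any analysis, and the analysing statistician stays blinded. A threshold fixed in that plan would be prespecified. The article simply does not name one.
- **That a loss of a third to a half of the information is built into the plan.** That range assumes normality and a cut leaving at least 20% on each side; a more extreme cut loses more. A mixed-effects ordinal logistic model would need no cut at all. Using the 3/π rank-test efficiency as an approximation, its power under the assumptions of step 4 would be about 52% against 54%. The text does not say ordinal, so it still needs repair.
- **That the model would suffer sparse-data bias.** No event rate is given and the covariates are deferred, so nothing in the article shows this.

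**Conclusion.** The point holds as a contradiction between adjacent sentences: a score outcome is paired with a model for a binary outcome, and no section supplies the endpoint that would reconcile them. It should be corrected before analysis, because it leaves the primary estimand undefined.

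The size is conditional. If the scores were dichotomised, the loss of information would be about 36% at best under normality, about half at a 20/80 split and two thirds at 10/90. Power would fall from about 54% to between 32% and 39% under the assumed ICC of 0.05 and effect of 0.5 SD. These figures illustrate the cost of one way of carrying out the sentence. They are not properties of the plan, and they are not a shortfall against any power the trial promised.

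**What to change.** Replace the model sentence. For each of the PHQ-8 and GAD-7, fit a linear mixed model to the 6-month score, with treatment arm, baseline score and the randomisation stratum (site) as fixed effects and clinician as a random effect. Use a small-sample degrees-of-freedom correction for the 18 clusters, for example Kenward-Roger or Satterthwaite. Report the adjusted mean difference with its 95% CI, and the ICC. Because the model adjusts for baseline, it also serves the Results section's description of the outcome as change.

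Make any responder analysis by logistic regression secondary, with its cut-off fixed in advance. If a binary or ordinal primary endpoint was in fact intended, define it in the Quantitative Data Analysis section, with the cut-off if it is binary, and align the outcome sentence with it.

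The essential correction is the model family or the endpoint definition; the exact covariates and the choice of correction can sit in the analysis plan. The cost is one sentence, plus a note in the analysis plan that it departs from the published wording. No new data are needed, and the named software, Stata, fits this model.
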